# Suction mini-percutaneous nephrolithotomy versus standard percutaneous nephrolithotomy for the management of 2–4 cm kidney stones: study protocol for an international, multicenter, parallel-group, noninferiority, randomized controlled trial

**DOI:** 10.1007/s00345-026-06302-7

**Published:** 2026-02-26

**Keywords:** Suction, Percutaneous nephrolithotomy, Mini PCNL, Renal stones

## Abstract

**Purpose:**

Percutaneous nephrolithotomy (PCNL) is recommended as the first-line treatment choice for the management of kidney stones larger than 2 cm. However, tract-related complications have always been a concern, especially in standard PCNL where a larger tract > 24Fr is established. The mini-PCNL technique with smaller tract (≤ 18 Fr) has been introduced to decrease tract related complications. Yet, with a smaller mini-PCNL tract, fragments must be fragmented into smaller pieces before extraction, potentially prolonging the operative time. Moreover, if the outflow of irrigation fluid is insufficient via the smaller tract, the intrarenal pressure (IRP) can build up, leading to pyelovenous backflow and infectious complications – an issue theoretically mitigated by the addition of suction techniques. However, high-level evidence comparing suction mini-PCNL outcomes to standard PCNL is still lacking.

**Methods:**

The present multicenter, international, randomized controlled noninferiority trial compares suction mini-PCNL to standard PCNL in the management of 2–4 cm kidney stones. The primary outcomes are the immediate postoperative stone-free rate (SFR) and operative time, while secondary outcomes include the final SFR at 1 month, postoperative pain score, length of hospital stay, postoperative complications, and quality of life.

**Results:**

A total of 960 patients from 20 urological centers will be randomized to receive either suction mini-PCNL or standard PCNL. Intention-to-treat analysis will be performed. For SFR, non-inferiority will be concluded if the lower bound of the 95% confidence interval for the absolute risk difference exceeds − 10%. For operative time, non-inferiority will be concluded if the lower bound of the 95% confidence interval for the mean difference exceeds − 10 min. For all other analyses, a two-sided p-value of < 0.05 will be regarded as statistically significant. Subgroup analyses will be performed to explore potential effect modification by stone location and stone density.

**Conclusion:**

The aim of this trial is to generate high-level evidence regarding the noninferiority of suction mini-PCNL compared to standard PCNL for 2–4 cm renal stones. The trial is registered on ClinicalTrials.gov as NCT05088213.

## Introduction

Percutaneous nephrolithotomy (PCNL) is recommended as the first-line treatment choice for kidney stones larger than 2 cm in international guidelines [1–3]. However, tract-related complications affecting renal parenchymal and blood vessels have always been a concern [4–6]. The mini-PCNL technique which uses a smaller tract (≤ 18 Fr) has been introduced to decrease tract-related complications [7–9]. Nevertheless, the smaller mini-PCNL tract necessitates fragmentation of stones into smaller pieces before extraction, potentially prolonging the operative time. Additionally, higher pressure irrigation is often required to flush out fragments by vacuum cleaner effect [10]. If the drainage of irrigation fluid is insufficient via a smaller tract, the intrarenal pressure (IRP) may build up, leading to pyelovenous backflow and infectious complications [11].

Suction application in mini-PCNL has the potential to enhance stone fragments removal efficiency, maintain low IRP, and decrease potential postoperative infection complications [12–14]. In the pre-suction era, mini-PCNL achieved noninferior stone-free rates (SFR) and operative times compared to standard PCNL, along with benefits of reduced bleeding, less postoperative pain, and shorter hospital stay [15]. However, high-level evidence regarding whether suction mini-PCNL can attain comparable outcomes to standard PCNL is still lacking.

Therefore, we have designed this multicenter, international, randomized controlled noninferiority trial comparing suction mini-PCNL with standard PCNL in the management of 2–4 cm kidney stones.

## Study objectives

The objective of the present study is to determine whether suction mini-PCNL is noninferior to standard PCNL in terms of surgical efficiency in the management of 2–4 cm kidney stones.

The primary outcomes are the immediate postoperative stone-free rate (SFR) and operative time. Secondary outcomes include the final SFR at 1 month, length of hospital stay, postoperative complications, and quality of life.

## Study design and methods

### Study overview

The present study is an international, multicenter, prospective, parallel group, noninferiority, randomized controlled trial.

### Setting

This study will be conducted in accordance with the principles of the Declaration of Helsinki. Approval was granted by the Medical Research Ethics Committee of The First Affiliated Hospital of Guangzhou Medical University: #2021(81). The study will be carried out in 20 urological institutes across the world, including 6 in Europe, 4 in America and 10 in Asia. Each participating urologist is required to possess significant experience of both suction mini-PCNL and standard PCNL, conducting ≥ 100 cases per annum.

### Sample size

The reported SFRs following suction mini-PCNL and standard PCNL for 2–4 cm renal stones are 83% and 86% respectively [3, 10, 13, 15]. We hypothesize that the SFR following suction mini-PCNL is noninferior to standard PCNL. The noninferiority margin is prespecified at -10%, based on clinical consensus and prior randomized controlled trial [15]. Assuming a one-sided α of 0.025, a power of 80%, and a noninferiority margin of -10% [15], the minimum required sample size per group is calculated to be 419. Considering an anticipated withdrawal and loss to follow-up rates of approximately 10%, this is adjusted to 480 participants per group, resulting in a total sample size of 960.

The reported operative times for mini-PCNL and standard PCNL in the management of 2–4 cm kidney stones are comparable [15]. Since suction mini-PCNL is faster than mini-PCNL [13], we conservatively assume that there is no difference in operative time between suction mini-PCNL and standard PCNL. The reported standard deviation is approximately 15 min [13, 16]. Our hypothesis is that the operative time for suction mini-PCNL is noninferior to that of standard PCNL. Assuming a one-sided α of 0.025, a power of 80%, and a noninferiority margin of -10 min, the minimum required sample size per group is calculated to be 43, which is smaller than the sample size determined based on SFR.

Thus, the final total sample size is set at 960.

### Patients population

The inclusion criteria are as follow: (1) Adults aged 18–70 years; (2) American Society of Anesthesiology (ASA) score of 1–2; (3) Kidney stones measuring 2–4 cm in diameter on non-contrast computer tomography; (4) Ability to provide written informed consent and adhere to trial requirements.

The exclusion criteria are as follow: (1) Anatomy abnormalities, such as urinary diversion, horseshoe kidney, transplanted kidney, or ureteropelvic junction obstruction; (2) Untreated acute urinary tract infection (UTI); (3) Patients on anticoagulant/antithrombotic therapy, or with uncorrected coagulopathies; (4) Patients who decline trial enrolment or cannot adhere to trial requirements.

### Screening and enrollment of participants

All participating centers will follow a standardized process to conduct this study. Clinicians or designated personnel will assess patients with suspected renal stones as part of routine clinical practice. Once renal stones are confirmed by CT scan and patients are fully evaluated for PCNL, eligible patients screened from the inclusion and exclusion criteria will be well informed of the trial and offered an information leaflet, detailing the potential benefits and drawbacks of the two different PCNL techniques. Patients will have ample opportunity to discuss with the local clinical team, and those who choose to participate will be able to do so. A log will be kept of all patients assessed to document reasons for their non-inclusion in the study to inform the CONSORT diagram. In addition to regular coverage, additional medical insurance and perioperative care would be provided for these candidates. Signed informed consent forms will be obtained from all participants prior to any study-specific procedures. Following consent, participants will be randomized to one of the two treatment groups.

### Randomization and allocation and blinding

Participants will be randomized in a 1:1 ratio to either standard PCNL or suction mini-PCNL. Stratified randomization will be performed according to the participating centers. Randomization sequence generation will be performed electronically using random block sizes of 4 and 6 prior to patient enrolment. Random sequence allocation and concealment will be implemented using consecutively numbered, opaque, tamper-proof envelopes.

Patients will be blinded to the intervention, however blinding of surgeons will not feasible due to the nature of the procedures. Radiologists evaluating the postoperative CT scans will be blinded to the intervention received. The postoperative clinical assessment will be performed by investigators blinded to the intervention and not involved in the surgical interventions. Blinded statistical analyses will be conducted with the code of intervention arm assignment remaining concealed until the analyses and interpretation have been completed.

### Surgical protocol

A standardized operative protocol will be established to ensure uniformity across all centers. Periodic protocol monitoring visits will be conducted to ensure its adherence at all participating centers.

#### Preoperative evaluation and preparation

In addition to the routine blood and urine examination, a non-contrast CT (NCCT) scan with 2 mm slice thickness is required for all patients. Stone characteristics, such as burden (largest diameter) and density (Hounsfield Unit, HU), will be measured from NCCT.

A single prophylactic antibiotic dose (200 mg cefuroxime or 500 mg levofloxacin, or according to local antibiograms at the discretion of the operating surgeon) will be administered to all patients 0.5 h before surgery. Patients with positive urine culture will receive culture-sensitive antibiotics for 5–7 days prior to procedure.

All procedures will be performed under general anesthesia. A 5Fr open-ended ureteral catheter will be inserted into the target ureter in lithotomy position, followed by a 16Fr Foley catheterization for bladder drainage. The patient will then be turned prone for PCNL access tract creation and lithotripsy.

#### PCNL procedures

Ultrasound-guided puncture to the target calyx will be performed using an 18-gauge coaxial needle. Retrograde pyelogram via the ureteral catheter will confirm the puncture position, followed by guidewire insertion. Tract dilatation over guidewire will be accomplished using fascial dilators.

For standard PCNL, 24Fr sheath will be inserted, and 20Fr nephroscope (Richard Wolf, Germany) will be used. Renal stones will be fragmented and aspirated using an ultrasonic-lithotripter (LithoClast Master, EMS or ShockPluse-SE, Olympus).

For suction mini-PCNL, 18Fr suction sheath (Wellead, China) will be inserted, and 12Fr mini-nephroscope will be used. Renal stones will be fragmented by pneumatic lithotriptor or Ho: YAG laser (1.0–2.0 J ×20–30 Hz), and stone fragments will be aspirated out via the suction sheath.

Upon conclusion of the procedure, fluoroscopy will be utilized to detect any residual stones. If present, further attempts, including the possible creation of additional tracts, will be made to remove all residual fragments. Double-J stent and/or nephrostomy tube will be inserted at the discretion of the operating surgeon. Tubeless PCNL may be feasible if there is no significant residual stone, bleeding, collecting system perforation, or ureteral obstruction.

### Postoperative evaluation and follow-up

Operative details including operative time will be timely documented. All intraoperative complications including bleeding, collecting system perforation, organ injury or other perioperative complications will be evaluated using the Clavien-Dindo grading system.

Complete blood count and electrolyte biochemical tests will be performed within 2 h after surgery. Patients with a hemoglobin level < 70 g/l will receive blood transfusion.

KUB will be obtained on the morning of postoperative day one to evaluate the stone-free status, stent and nephrostomy tube status. A low-dose NCCT scan with 2 mm slice thickness will be conducted within 72 h after the operation to evaluate the postoperative immediate SFR. If residual fragments ≧4 mm are present, any information concerning auxiliary treatments will be recorded, including the size of residual stones, type of auxiliary treatment and final outcome.

If nephrostomy tube is placed, it will be removed in the absence of significant bleeding or complications, followed by patient discharge. The double-J stent will be removed after 2 weeks.

Pain visual analog scale (VAS) will be evaluated at three time points, namely pre-operatively, post-operatively 6 h, and follow up at 1 month respectively. Postoperative analgesia requirement will be documented to reflect postoperative pain and recovery. Quality of life (QoL) scores will be assessed by Wisconsin Stone Quality of Life questionnaire (WISQOL) pre-operatively, as well as 4 weeks postoperatively [17].

### Data collection and statistical analysis

#### Data collection and quality control

Patients’ demographics and all clinical outcomes will be recorded in the pre-established case report forms (CRF). Two urologists will take turns recording and verifying work for each recruited case. The data of each participating center will be uploaded and summarized weekly, and on-site verification will be conducted periodically to ensure data authenticity and accuracy. Reassessment will be required if summarized data deviate significantly from the median level in the preliminary statistics analysis.

Stone-free status will be evaluated by blinded radiologist from 2 mm slice NCCT scan performed postoperatively within 72 h and at 1 month. Stone size will be defined as the largest diameter for a single stone or the sum of the largest diameters for multiple stones. Stone size and Hounsfield units (HU) will be measured consistently using the same software across all centers. S.T.O.N.E. score will be used for evaluation of stone complexity [18]. Operative time will be calculated from the percutaneous puncture to completion of double-J or nephrostomy tube placement. Hospital stay will be calculated from the day of surgery to the day of discharge and rounded up to the nearest whole day. Intraoperative and postoperative complications will be documented and graded according to the Clavien-Dindo classification.

Each recruited case will have three CRFs completed by its participating center: one at randomization, one after the intervention, and one at 1-month follow-up, including details of any additional interventions and complications. Table 1 outlines the schedule for outcome assessment and data collection (Fig. 1).

**Table 1 Tab1:** Schedule for data collection and outcome assessment

Outcome measure	Timing				
	Recruitment	Intervention			Follow-up
		Intraoperative	Postoperative	Upon discharge	1 month
Baseline assessment					
Age	√				
Stone size	√				
ASA score	√				
Laboratory tests	√		√		√
Stone evaluation					
KUB X-Ray	√		√		
NCCT	√		√		√
Quality of life score	√				√
Pain score	√		√		√
Operative characteristics					
Operation time		√			
Puncture guidance		√			
Puncture site		√			
Tract size		√			
Tract number		√			
Tube status		√			
Hospital stay				√	
Complications					
Bleeding		√	√		
Infection		√	√		
Organ injury		√	√		
Others		√	√		√
Immediate stone-free status			√		
Final stone-free status					√

*ASA * American Society of Anesthesiologists, *KUB* kidney ureter bladder, *NCCT* non contrast computer tomography

#### Study flow chart

**Fig. 1 Fig1:**
[figure not shown]
Study flow chart. *PCNL* percutaneous nephrolithotomy, *QOL* quality of life, *SFR* stone-free rate, *Hgb* hemoglobin, *Scr* serum creatinine

#### Outcome measures

##### Primary outcomes

The co-primary outcomes are the immediate postoperative stone-free rate (SFR) and operative time. Immediate postoperative SFR is defined as the absence of residual stone or fragments < 2 mm on low-dose NCCT scan within 72 h after operation. Operative time is defined as the time from percutaneous puncture to completion of double-J or nephrostomy tube placement.

Secondary outcomes are as follows: Final SFR: defined as no residual stone or fragments <2 mm on NCCT (2 mm slice) at 1 month post intervention.Pain VAS score.Length of hospital stay: calculated from the day of surgery to the day of discharge, rounded to the nearest whole day.Postoperative complications up to 1 month post-intervention, evaluated using the Clavien-Dindo classification.QoL will be assessed preoperatively and at 1 month postoperatively by the WisQoL questionnaire.

#### Statistical analysis

Intention-to-treat analysis will be performed. All enrolled participants with complete data will be included in the analysis. Statistical analyses will be conducted using Statistical Package for Social Sciences (SPSS) 22.0 or above and R software version 4.3.1 or above (R Foundation for Statistical Computing). Continuous data will be presented as median (IQR) and analyzed using Student’s t test or Mann-Whitney U test, as appropriate. Categorical data will be expressed as n (%) and compared using the χ2 test or Fisher’s exact test, as appropriate.

Pre-specified sensitivity analyses will be performed to assess the robustness of the primary findings under alternative, clinically plausible noninferiority margins. These sensitivity analyses will include SFR noninferiority margins of − 5% and operative time noninferiority margins of − 5 and − 10 min, respectively. These analyses will be exploratory in nature and are intended to evaluate the consistency of conclusions across different noninferiority thresholds, rather than to redefine the primary hypotheses or decision criteria. Subgroup analyses will be performed to explore potential effect modification by stone location, stone density and lithotripsy energy modality. Logistic regression and linear regression models including a treatment-by-subgroup interaction term will be used to evaluate the interaction effect on SFR and operative time, respectively.

This trial includes two co-primary endpoints: postoperative SFR and operative time. To control the overall type I error rate, a joint noninferiority testing strategy based on the intersection–union principle will be applied. Noninferiority of suction mini-PCNL will be concluded only if both co-primary endpoints independently satisfy their respective noninferiority criteria. Specifically, for SFR, non-inferiority is defined if the lower bound of the 95% confidence interval for the absolute risk difference exceeds − 10%. For operative time, non-inferiority is defined if the lower bound of the 95% confidence interval for the mean difference exceeds − 10 min. For all other analyses, a two-sided p-value of < 0.05 will be regarded as statistically significant.

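### The primary analysis is labelled intention-to-treat but limited to participants with undefined complete data, so randomised patients can be dropped with a bias of unknown size and direction

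*Protocol article*

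**What the plan says.** Under Statistical analysis, the protocol article gives the label and then the rule in consecutive sentences: "Intention-to-treat analysis will be performed. All enrolled participants with complete data will be included in the analysis". The abstract (Results) gives the label alone and goes straight on to the decision rule: "Intention-to-treat analysis will be performed. For SFR, non-inferiority will be concluded if the lower bound of the 95% confidence interval".

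The article does not say which data must be complete. Data collection and quality control provides three case report forms per patient: at randomisation, after the intervention and at 1 month. Both co-primary outcomes are available well before the third form. SFR is read on a CT within 72 h, and operative time is recorded during surgery.

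Under Sample size, the plan allows for attrition: "Considering an anticipated withdrawal and loss to follow-up rates of approximately 10%, this is adjusted to 480 participants per group".

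The robustness analyses are described thus: "Pre-specified sensitivity analyses will be performed to assess the robustness of the primary findings under alternative, clinically plausible noninferiority margins". They use -5% for SFR and -5 and -10 min for operative time. The primary margins are -10% and -10 min.

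**The concern.** An intention-to-treat set contains everyone randomised, in the arm allocated. A set limited to participants with complete data does not. The article states both, so this is a contradiction in a stated rule and not a detail left to another document. An analyst who follows the second sentence removes randomised patients, while a reader of the abstract believes that none were removed.

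Two things follow. First, because the term is undefined, the rule could discard patients whose co-primary outcomes are both known, only because a later form is missing. Second, if the dropped patients differ from the others, and differ by another amount in each arm, the estimated SFR difference shifts. The decision turns on whether a confidence limit clears -10 points, so a shift of two or three points can change the conclusion. The sensitivity analyses named in the article compare the same interval with other thresholds. None changes who is analysed or how missing outcomes are treated, and the -10 min one repeats the primary criterion.

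**Working it through.** **Inputs from the article (Sample size).** SFR for suction and standard "are 83% and 86% respectively"; margin -10 points; one-sided alpha 0.025; power 80%; 419 per group before and 480 after an allowance of about 10%.

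**The plan's own figure.** n = (1.960 + 0.842)² × [0.83×0.17 + 0.86×0.14] / (0.10 - 0.03)² = 7.849 × 0.2615 / 0.0049 = 418.9, so 419 per group. This reproduces. Dividing 419 by 0.90 gives 466. The stated 480 is a little more generous, equal to an allowance of 1 - 419/480 = 12.7%.

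**Effect of the complete-data rule on false non-inferiority for SFR.** Assume that the truth among all randomised patients is exactly at the margin: standard 86%, suction 76%. Let a share m of each arm be missing, with stone-free rate q among the missing. The complete-case rate in an arm is

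p_obs = (p_true - m × q) / (1 - m),

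and, with 480 × (1 - m) patients per arm and a Wald interval,

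P(conclude non-inferiority) = Φ[(difference + 0.10)/SE - 1.96].

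Example with m = 10% (432 per arm), q = 50% for suction and 86% for standard:
- suction p_obs = (0.76 - 0.05)/0.90 = 0.789; standard stays at 0.860; difference -0.071
- SE = √[(0.789×0.211 + 0.86×0.14)/432] = 0.0258
- P = Φ(0.0289/0.0258 - 1.96) = Φ(-0.84) = 20.1%

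The same formula gives the table below. The values of m and q are assumptions, since the article gives none for the co-primary outcomes.

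| Missing per arm | Stone-free among missing, suction / standard | Complete-case difference (points) | False non-inferiority on SFR |
|---|---|---|---|
| 10% | 76% / 86% (unrelated to outcome) | -10.0 | 2.5% |
| 10% | 50% / 86% | -7.1 | 20.1% |
| 10% | 60% / 86% | -8.2 | 10.1% |
| 10% | 50% / 60% | -10.0 | 2.5% |
| 10% | 50% / 50% | -11.1 | 0.8% |
| 3% | 50% / 86% | -9.2 | 5.0% |
| 3% | 60% / 86% | -9.5 | 3.9% |
| 2% | 50% / 86% | -9.5 | 4.0% |
| 2% | 60% / 86% | -9.7 | 3.4% |

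**Can the handling rule alone reverse a result?** Take 480 per arm with 10% of suction and 5% of standard missing (assumed), and about 83% and 86% stone-free among those observed.
- Complete cases: 359/432 against 392/456, difference -2.9 points, lower 95% limit -7.6 (non-inferior).
- Missing counted as not stone-free: 359/480 against 392/480, difference -6.9 points, lower limit -12.1 (not non-inferior).

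With 10% missing in both arms the two limits are -7.8 (359/432 against 372/432) and -8.1 (359/480 against 372/480), and nothing changes. What matters is the imbalance between arms.

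**Power if everyone is analysed.** At 83% against 86%, SE = √(0.2615/480) = 0.0233 and power = Φ(0.07/0.0233 - 1.96) = 85.1%. With 432 per arm it is 81.2%.

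**The case against.** The strongest reply has three parts.

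- **Direction.** A reader might infer that dropping patients favours non-inferiority. The document does not support that. The inflated rates require missing suction patients to do much worse than other suction patients while missing standard patients do as well as the rest of their arm. If the missing are worse in both arms and still 10 points apart, there is no bias. If both are at 50%, the test becomes conservative. This part of the reply stands.
- **Amount missing.** The figure of about 10% is for withdrawal and loss to follow-up, whereas SFR is read within 72 h and operative time is recorded in theatre. Missing co-primary data may be far below 10%, and at 2-3% the two unfavourable scenarios give only 3.4% to 5.0%. This stands too, unless complete data also requires the 1-month form. The text leaves that open, and the ambiguity is itself part of the problem.
- **What is not shown.** A reader might also infer that no per-protocol or missing-data analysis is planned. The article names none, but a condensed article commonly leaves these to the full protocol or analysis plan, so their absence here is not a finding.

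None of this removes the contradiction. The article states the complete-data rule directly after the intention-to-treat label, and any fuller document that follows the article would carry the rule over.

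**Conclusion.** The point holds in this form: the stated primary analysis set contradicts its label, its key term is undefined, and the listed sensitivity analyses cannot reveal the effect because they change only the threshold. The consequence for the conclusion is of unknown size and direction. With the truth at the margin, false non-inferiority on SFR runs from 0.8% to 20.1% over the scenarios with 10% missing per arm, and from 3.4% to 5.0% in the unfavourable scenarios with 2-3% missing, against a nominal 2.5%. These figures rest on assumed missing-data rates and assumed outcomes among the missing. They concern SFR alone; the joint rule also requires operative time to succeed, so they are not error rates for the trial's overall claim. The sample size of 419 per group is reproduced and is not in question. The wording should be corrected before the data are unblinded, but the document does not show that the analysis is biased towards success.

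**What to change.** Replace the second sentence with:

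*All randomised participants are analysed in the arm allocated. Each co-primary endpoint uses every participant with that outcome, whether or not 1-month data are complete. Missing 72 h SFR or operative time is multiply imputed by arm using centre, stone size, HU and S.T.O.N.E. score.*

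Replace the duplicate -10 min sensitivity analysis with a tipping-point analysis that varies the SFR of missing patients separately in each arm and reports where the conclusion changes. This is needed because standard multiple imputation assumes that missingness is explained by the covariates used. Counting every missing suction patient as a failure would be one extreme of that range, not a substitute for it.

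Report a per-protocol analysis for both co-primary endpoints as supportive. Making its agreement a second condition for success would be a design choice with a power cost, and this point does not call for it. If a fuller plan already contains these analyses, it is enough to correct the article's sentence and align the two documents.

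The cost is wording, some extra programming and possibly a slightly wider interval. No extra patients are needed: at the planned rates power is about 85% if all 480 per arm are observed and about 81% with 432.

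### Randomisation is stratified by centre and useful baselines are collected, but every between-arm test named is unadjusted: valid and slightly conservative, with some precision given up for nothing

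*Protocol article*

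**What the plan says.** All references are to the Protocol article.

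- Setting: "The study will be carried out in 20 urological institutes across the world".
- Randomization and allocation and blinding: "Stratified randomization will be performed according to the participating centers". Allocation is 1:1, and "Randomization sequence generation will be performed electronically using random block sizes of 4 and 6 prior to patient enrolment".
- Preoperative evaluation and preparation, and Table 1: stone size and density are measured before surgery in all patients.
- Postoperative evaluation and follow-up: pain VAS is taken before surgery, at 6 h and at 1 month. "Quality of life (QoL) scores will be assessed by Wisconsin Stone Quality of Life questionnaire (WISQOL) pre-operatively, as well as 4 weeks postoperatively".
- Statistical analysis: "Continuous data will be presented as median (IQR) and analyzed using" the t test or Mann-Whitney test; "Categorical data will be expressed as n (%) and compared using the" chi-square or Fisher test. The primary decisions rest on 95% confidence intervals for an absolute risk difference (SFR) and a mean difference (operative time), with no centre or baseline term given for either. Regression is named only for treatment-by-subgroup interactions.

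**The concern.** Small blocks within centre keep the arms almost perfectly balanced in each centre, so differences between centres largely cancel out of the treatment contrast. An unadjusted standard error still counts those differences as noise. The interval then no longer matches the randomisation and is wider than it need be. Some centre variation is plausible: the Discussion itself concedes possible heterogeneity in patient selection, energy modality and surgeon experience.

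Separately, stone size is likely to predict clearance and operative time, and a patient's pre-operative VAS or WISQOL is likely to predict the later score. Leaving them out discards information that the trial pays to collect. At stake is precision, mainly for SFR (the endpoint that drives the sample size) and for pain and quality of life.

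**Working it through.** **Inputs from the Protocol article.** SFR 83% (suction mini-PCNL) and 86% (standard), margin −10 points, one-sided α 0.025, 80% power, 419 per group raised to 480 for about 10% loss, and operative-time SD 15 min (Sample size); 20 centres (Setting); blocks of 4 and 6 within centre (Randomization and allocation and blinding).

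**Assumptions; the document gives no values.** Between-centre share of variance (ICC, ρ) 0 to 0.20; centre logit SD for SFR 0.4 to 1.0; baseline correlation r for VAS and WISQOL 0.3 to 0.7.

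**1. The plan's own figure.** n = (1.96 + 0.8416)² × (0.83×0.17 + 0.86×0.14) / (0.10 − 0.03)² = 7.849 × 0.2615 / 0.0049 = 418.9, so 419 per group. This is the unadjusted two-proportion formula, so the planned 80% is already the power of an unadjusted analysis. With 432 analysed (480 less 10%), s = √(0.2615/432) = 0.0246, the 95% half-width is 4.82 points, and power is Φ(0.07/0.0246 − 1.96) = 81.2%.

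**2. Ignoring centre.** With blocking within centre, the true variance of the difference is about (1 − ρ) times the unadjusted variance. So:

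- coverage of the unadjusted interval = 2Φ(1.96/√(1−ρ)) − 1
- one-sided error = 1 − Φ(1.96/√(1−ρ))
- SFR power, unadjusted = Φ((0.07 − 1.96s) / (s√(1−ρ)))
- SFR power, centre-adjusted = Φ(0.07/(s√(1−ρ)) − 1.96)

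At 432 per group:

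| ρ | Coverage | One-sided error | SFR half-width, unadj → adj (points) | Operative-time half-width, unadj → adj (min) | SFR power, unadj → adj |
|---|---|---|---|---|---|
| 0 | 95.0% | 0.025 | 4.82 → 4.82 | 2.00 → 2.00 | 81.2% → 81.2% |
| 0.05 | 95.6% | 0.022 | 4.82 → 4.70 | 2.00 → 1.95 | 81.8% → 83.1% |
| 0.10 | 96.1% | 0.019 | 4.82 → 4.57 | 2.00 → 1.90 | 82.5% → 85.1% |
| 0.20 | 97.2% | 0.014 | 4.82 → 4.31 | 2.00 → 1.79 | 83.9% → 88.9% |

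A simulation of a continuous outcome (20 centres of 48, blocks of 4 and 6, 2,500 runs per ICC) gave unadjusted coverage of 95.5%, 96.0% and 97.1% at ρ = 0.05, 0.10 and 0.20, and about 95% with centre adjustment.

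**3. SFR simulated directly as a binary outcome.** With 20 centres of 24+24 (480 per arm), overall rates held at 83% and 86%, and centre effects on the logit scale, power unadjusted versus stratified is:

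- logit SD 0.4: a gain of about 0.4 points
- logit SD 0.8: 85.2% vs 86.9%, a gain of 1.7 points
- logit SD 1.0: 86.0% vs 88.3%, a gain of 2.3 points

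With no centre variation, power is 85.1% either way. These gains are smaller than the last row of the table because ρ = 0.20 is a stronger centre effect than logit SD 1.0.

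**4. Baseline VAS and WISQOL.** Adjusting for the pre-operative score multiplies the interval width by √(1 − r²): 0.954, 0.866 and 0.714 for r = 0.3, 0.5 and 0.7. The interval narrows by about 5%, 13% and 29%.

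**The case against.** **The planned power is untouched.** A reader might infer that part of the 80% SFR power is lost. It is not: 419 comes from the unadjusted formula, and with centre variation the power of the unadjusted analysis rises slightly (81.2% to 83.9% in the table). A simulation can seem to show a loss if 83% and 86% are entered as the rates of the median centre. The overall rates then drop to about 80% and 83%, and power falls because those are no longer the plan's rates.

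**The error is conservative.** It cannot create a false claim of noninferiority. A reader might also infer that all the error bars are wrong. Only ignoring the randomisation strata affects coverage. Omitting stone size or a baseline score leaves the interval valid.

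**Operative time has precision to spare.** The unadjusted half-width is 2.0 min against a 10 min margin, so adjustment will not change that decision.

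**The method for the primary intervals is not stated.** The named tests stand in a general sentence, and the noninferiority rule is set out separately. An unseen analysis plan could specify a stratified interval. It is also tempting to say that the listed tests cannot deliver the decision intervals. That is true of Mann-Whitney, chi-square and Fisher as tests, but the t test, also listed, does give a mean-difference interval, and the risk-difference rule stands on its own.

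The first three points limit the size, and they stand. The last does not remove the point: the article names its between-arm methods, all of them unadjusted, and gives regression only for subgroups. As published, the plan does not use its stratification.

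**Conclusion.** The point holds as a free improvement, not as an error that threatens the trial's conclusion. If centres differ, the unadjusted intervals are somewhat too wide: coverage is about 95.6% to 97.2% and one-sided error about 0.022 to 0.014 for an assumed ICC of 0.05 to 0.20. The SFR gain forgone is about 0.4 to 2.3 power points, for an assumed centre logit SD of 0.4 to 1.0, overall rates of 83% and 86%, and 480 per arm. It is zero if centres do not differ. For VAS and WISQOL the interval would narrow by about 5%, 13% or 29% at an assumed baseline correlation of 0.3, 0.5 or 0.7. The ICC, logit SD and correlations are all assumptions, because the document gives none of them.

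**What to change.** Before the treatment code is opened, state in the analysis text:

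- SFR: base the decision on a centre-stratified (Mantel-Haenszel) risk difference, or on a standardised risk difference from a logistic model with centre and stone size, with its 95% CI.
- Operative time: base the decision on the mean difference and 95% CI from a linear model with treatment, centre and stone size.
- VAS and WISQOL: ANCOVA with the pre-operative score and centre.
- Keep the unadjusted tests as supportive analyses.

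The cost is wording only. Every variable is already collected, and the sample size does not change.
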